### Aim 3: Pilot RCT of adapted TSC

#### Aim 3 participants and randomization

We will recruit 75 adolescents (at least 35% self-identifying as Black; 10% self-identifying as Latinx) to participate in the RCT comparing the adapted TSC intervention plus Sleep Feedback (TSC + Sleep Feedback, described below) to a Sleep Feedback Only condition. Study inclusion/exclusion criteria are identical to those in Aim 1. Adolescents will be eligible to enroll in the study while engaged in other behavioral/mental healthcare and/or taking any sleep medications, which we will track.

Adolescents will be randomized using 2:1 allocation (2 TSC + Sleep Feedback: 1 Sleep Feedback Only) using a modification of Efron's biased coin toss procedure (98). We selected unequal allocation to maximize critical information about the intervention (e.g., adverse events). Random assignment will balance groups on age (middle vs. high school, since school start times typically shift earlier and social pressures further shorten sleep duration in high school), suicide risk (ideation/attempt history), and racial and ethnic background.

#### Aim 3 measures

Primary Aim 3 outcomes are related to TSC implementation, and include intervention feasibility, acceptability, appropriateness, and fidelity. Secondary Aim 3 outcomes are adolescent sleep disturbances, depressive symptoms, STB, and affective and behavioral regulation; the last of these are hypothesized intervention mechanisms (Figure 1). Sleep will be objectively assessed using actigraphy, which adolescents will wear throughout the TSC intervention period, with an accompanying daily diary to assess self-reported sleep, mood, and stressors (described below). All other secondary outcomes will be collected at baseline (pre-intervention) and at months 1, 3, 6, and 12. The type, frequency, and/or dose of behavioral, sleep, psychiatric treatment and/or medications will also be measured throughout the study using the Child and Adolescent Services Assessment (CASA) (99) throughout the study. Specific primary and secondary measures are as follows:

*Intervention acceptability* will be measured using the adolescent self-reported AIM (89) instrument, described in Aim 2. To further assess acceptability, adolescents will also complete the Client Satisfaction Questionnaire (CSQ) (100), adapted for the current study, as well as a semi-structured qualitative interview, with questions about TSC as described for the Aim 2 post-intervention interviews.

*Intervention feasibility* will be assessed through multiple methods (90), including *via* engagement (TSC sessions attended and attrition) and intervention fidelity assessments described for Aim 2. Adolescents will also complete the Intervention Appropriateness Measure (IAM) and the Feasibility of Intervention Measure (FIM) (89) to further assess perceived fit and feasibility of the intervention for addressing their sleep disturbances, respectively.

*Actigraphy* will be used to evaluate behavioral sleep and circadian characteristics, with the same procedures for implementation and scoring as in Aim 2. Outcomes for actigraphy-derived sleep disturbances are duration, regularity, and timing. Consistent with Study 1, a sleep diary will be used to complement actigraphy metrics for scoring purposes. The sleep diary will include time in and out of bed, sleep onset latency, night awakenings, and sleep quality (94). The sleep-specific diary questions will be sent *via* SMS text messages to participants each morning. See below for additional diary items administered in the evening.

*Daily mood and stressors* will be measured *via* adolescent self-reported daily diary items implemented during the TSC intervention period. These items will be deployed using links to a web-based form sent *via* SMS texts or emails, as in the sleep diary implementation. These items will be assessed in the evening and will include ratings of adolescents' mood; experiences of racism, discrimination, and victimization (101); and affective and behavioral regulation (impulsivity and reactivity to the day's most positive and negative event as in our prior work) (102).

*Weekly self-reported suicidal ideation and behavior* will also be rated *via* SMS using items modeled after the Columbia—Suicide Severity Rating Scale (C-SSRS) (103, 104).

*Weekly affective and behavioral regulation*, which are hypothesized intervention mechanisms, will also be measured through adolescent self-report using the Childhood Affective Lability Scale (CALS) (105) to assess affective regulation and the short UPPS-P Impulsive Behavior Scale (IBS) (106) for behavioral regulation.

*Self-reported sleep disturbances* will be measured at baseline and follow-up assessments using the PROMIS Sleep Disturbance and Sleep-Related Impairment Scales (97), as in Aim 2.

*Self-reported depressive symptoms and STB* will also be measured at baseline and follow-up assessments using the adolescent PHQ-9-M (81) and the C-SSRS, (103, 104) respectively.

#### Aim 3 intervention procedures

Intervention training and implementation procedures for TSC will be as described for Aim 2. The Sleep Feedback Only condition consists of reports summarizing prospectively gathered actigraphy and diary data. With the mass availability of wearable devices (e.g., Fitbit) and apps, such personalized sleep tracking is now widely accessible. However, despite increasing users' awareness of sleep habits, this approach yields minimal change in sleep behavior (107, 108). Thus, the Sleep Feedback Only comparator group controls for common receipt of information related to sleep behaviors while enabling us to focus on TSC adaptations to optimize ultimate implementation. These Sleep Feedback reports will be accessible to participants *via* web link sent weekly by SMS. Sleep Feedback reports will also be accessible to TSC clinicians *via* a HIPAA-secured online portal to inform selection and personalization of TSC modules.

#### Aim 3 analytic approach

As Aim 3 is a pilot study, sample size considerations center on the precision of confidence interval (CI) width estimation for implementation and target outcomes. Based on best practices for pilot studies (109, 110), given our intervention sample size (TSC + Sleep Feedback) of 50 and 5% type I error rate, we will be able to estimate 95% CI widths of no more than 0.28 for primary implementation and target outcomes.

Using descriptive statistics, we will compute the proportion (and 95% confidence intervals) of participants with high ratings for TSC feasibility (session attendance >80%, attrition < 20%; FIM >80%), acceptability (AIM >80%) and appropriateness (IAM >80%). We will examine these outcomes overall and according to participant racial and ethnic groups. For implementation outcomes with both quantitative and qualitative data (feasibility, acceptability, and appropriateness), we will use established approaches for analyzing mixed methods data described as in Aim 1. We will compare participants across cells on clinical and socio-demographic baseline characteristics using standard univariate statistics.

Additionally, we will assess whether improvements in sleep (*via* actigraphy-derived duration, regularity, timing; and *via* daily diary and PROMIS measures), depressive symptoms (PHQ-9-M), and risk for STB (C-SSRS), are greater among youth randomized to TSC + Sleep Feedback vs. Sleep Feedback Only conditions using linear mixed models. Exploratory analyses will examine putative intervention mechanisms (affective/behavioral dysregulation; Figure 1) based on daily diary, CALS, and IBS ratings. Study arm, time, and their interaction will be included as primary predictors, with random effects for study subject.

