#### Aim 2 measures

The primary Aim 2 outcomes pertain to intervention acceptability and feasibility. We will also pilot the sleep data collection methods and strategies to increase morning bright light and decrease evening light in anticipation of the Aim 3 randomized trial. Adolescents will wear actigraphs, Re-Timer glasses in the morning, blue-blocker glasses in the evening, complete a daily sleep diary, and provide ratings of their perceived sleep disturbances at pre and post intervention.

*Intervention acceptability* will be assessed at post-intervention using the adolescent self-reported Acceptability of Intervention Measure (AIM) (89). We will also conduct semi-structured qualitative interviews to identify participants' perspectives about intervention acceptability, barriers, and recommendations for additional adaptations to content or delivery strategies.

*Intervention feasibility* will be indexed by multiple outcomes (90), including the number of TSC sessions attended and rates of intervention attrition, to index intervention engagement. Intervention fidelity will be measured *via* the coding of a randomly selected 10% of video recorded TSC sessions. Sessions will be coded using the Cognitive Therapy Scale (CTS) (91) and a TSC session checklist (92), both used in prior TSC research.

*Actigraphy* is a widely used method of assessing sleep and circadian disruptions longitudinally in an individual's natural environment. Actigraphy is well-validated validated against polysomnography, the gold standard measure of overnight sleep (93). Consistent with guidelines, adolescents will continuously wear an actigraph on their non-dominant wrist, unless bathing or swimming, and complete a corresponding sleep diary for actigraphy scoring purposes. Sleep diary ratings will include time in and out of bed, sleep onset latency, night awakenings, and sleep quality (94). Actigraphy data will be scored using the Cole-Kripke algorithm in ActiLife software, which are validated against polysomnography and other actigraphs in young adults (95) and adolescents (96).

*Self-reported sleep disturbances* will be measured using the well-validated pediatric Patient-Reported Outcomes Measurement Information Systems (PROMIS) Sleep Disturbance and Sleep-Related Impairment Scales (97), which respectively measure perceived sleep difficulties and the impacts of sleep on daily functioning.

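### The 0.28 confidence-interval width that justifies the Aim 3 sample size holds for single-arm proportions, not for the between-arm target outcomes

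*Protocol article*

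**What the plan says.** All references are to the Protocol article.

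- Aim 3 participants and randomization: "We will recruit 75 adolescents", and "Adolescents will be randomized using 2:1 allocation (2 TSC + Sleep Feedback: 1 Sleep Feedback Only". This gives 50 and 25.
- Aim 3 analytic approach: "sample size considerations center on the precision of confidence interval (CI) width estimation for implementation and target outcomes". The figure is derived "given our intervention sample size (TSC + Sleep Feedback) of 50 and 5% type I error rate", and the result is that "we will be able to estimate 95% CI widths of no more than 0.28 for primary implementation and target outcomes". No scale is attached to 0.28, and no allowance is made for missing data.
- Aim 3 measures: "Primary Aim 3 outcomes are related to TSC implementation, and include intervention feasibility, acceptability, appropriateness, and fidelity". Sleep, depressive symptoms, STB and affective and behavioral regulation are secondary.
- Aim 3 analytic approach, on estimands: feasibility, acceptability and appropriateness are to be summarised as proportions with 95% intervals. Sleep, PHQ-9-M and C-SSRS results are to be compared between the two arms by linear mixed models with arm, time and their interaction.

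The term target outcomes is not defined. I read it as the sleep, depression and STB outcomes, because the sentence sets it beside the implementation outcomes and these are the other outcomes that the section analyses.

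**The concern.** One number is offered for two kinds of quantity. The first is a proportion in one arm of 50, bounded between 0 and 1. The second is a difference in improvement between 50 and 25 participants, mostly on continuous scales. A bound that suits the first has no reason to suit the second: the smaller arm dominates the standard error, and the unit changes from a probability to a standard deviation.

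This is the only quantitative justification given for the size of the RCT, and the Discussion says that the results will inform a fully powered trial. A reader who takes 0.28 at face value for the clinical outcomes would think the efficacy estimates much firmer than the design can make them.

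**Working it through.** **Inputs.** TSC arm 50 and comparator 25 (75 at 2:1); 95% intervals, z = 1.96; stated width at most 0.28; attrition benchmark below 20% (Aim 3 analytic approach), taken here as 40 of 50 and 20 of 25. The article gives no SD or correlation, so continuous outcomes are in SD units and correlations are assumptions.

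**1. The stated figure.** One proportion, Wald, worst case p = 0.5:

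2 × 1.96 × √(0.25/50) = 0.277, which rounds to 0.28.

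Other interval methods with n = 50 have maximum widths close to this: Wilson 0.267, Jeffreys 0.271, Clopper-Pearson 0.290. For a single-arm proportion the figure is sound.

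**2. The same figure with fewer raters.** With 40 observed:

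- p = 0.5: 2 × 1.96 × √(0.25/40) = 0.310
- p = 0.8: 2 × 1.96 × √(0.16/40) = 0.248

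**3. A continuous outcome in the TSC arm alone.** 2 × 1.96/√50 = 0.554 SD. The value 0.28 SD is the half-width here, not the width.

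**4. A continuous outcome between arms, unadjusted, one time point.**

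- 50 vs 25: 2 × 1.96 × √(1/50 + 1/25) = 3.92 × 0.2449 = 0.960 SD
- 40 vs 20: 2 × 1.96 × √(1/40 + 1/20) = 3.92 × 0.2739 = 1.074 SD

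**5. Using the baseline value.** With baseline adjustment the width is multiplied by √(1 − r²); for a difference in change scores, by √(2(1 − r)).

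| Assumed r | Adjusted, 50 vs 25 | Adjusted, 40 vs 20 | Change score, 50 vs 25 |
|---|---|---|---|
| 0.5 | 0.83 SD | 0.93 SD | 0.96 SD |
| 0.7 | 0.69 SD | 0.77 SD | 0.74 SD |
| 0.8 | 0.58 SD | 0.64 SD | 0.61 SD |

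To reach 0.28 SD with full data, baseline adjustment would need r = √(1 − (0.28/0.960)²) = 0.957.

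**6. Using all follow-ups.** As a favourable case, assume that the effect is averaged over the four follow-ups (months 1, 3, 6 and 12), adjusted for baseline, with equal correlation r between all visits. The multiplier is √((1 + 3r)/4 − r²).

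- r = 0.5: √(0.625 − 0.25) = 0.612, width 0.59 SD
- r = 0.8: √(0.85 − 0.64) = 0.458, width 0.44 SD

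The article does not name this estimand; the case only shows that repeated measures do not close the gap.

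**7. A binary outcome between arms.** 2 × 1.96 × √(p(1 − p)(1/50 + 1/25)):

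- p = 0.5: 0.480
- p = 0.8: 0.384

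This is the only between-arm case on the same scale as 0.28. It is 0.384/0.28 = 1.4 to 0.480/0.28 = 1.7 times as wide.

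**The case against.** The best defence is that nothing was miscalculated. The sentence ties 0.28 to the 50 in the TSC arm, it does not promise that width for a comparison of 50 with 25, and target outcomes is undefined. The clinical outcomes are secondary in a declared pilot, no power is claimed, and detailed precision for each contrast may stand in a fuller document. It is true that the arithmetic is right for a proportion and that the fault is one of scope. But the sentence names target outcomes, the section analyses the clinical outcomes only between arms, and a mean in the TSC arm alone also misses the figure (0.55 SD). The sentence would be right only if those outcomes were dichotomised and reported in one arm, and no such analysis is described. An overstated claim in the article is not cured by detail elsewhere.

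Several stronger readings are tempting, and the documents do not support them:

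- **That 0.28 needs all 50 observed.** This is so only near p = 0.5. Around the plan's own 80% marks, 40 raters give 0.248. Attendance and attrition can be scored on everyone randomized; the AIM, FIM and IAM ratings are the ones exposed to missing data.
- **That 0.28 fails for fidelity, because it rests on "the coding of a randomly selected 10% of video recorded TSC sessions".** The Aim 2 sections describe scores on a rating scale and a checklist, and Aim 3 analytic approach lists no proportion for fidelity. Without a stated summary and its SD, no width follows.
- **That 0.28 is promised for subgroups.** The article says "We will examine these outcomes overall and according to participant racial and ethnic groups", but it ties the figure to 50 participants. The Discussion also concedes the small samples.
- **That the clinical estimates are more than three times less precise than stated.** This divides SD units by a probability width.
- **That the next trial will be sized from this trial's point estimates.** The Discussion says only that results will inform it.

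**Conclusion.** The point holds in a limited form. The 0.28 figure is correct as the worst-case width for a single-arm proportion with 50 observed, and wrong as a statement about the target outcomes. For a between-arm difference on a continuous scale, the reference value is 0.96 SD: unadjusted, one time point, full data. It is not a forecast for the planned mixed model. Losing 20% in each arm raises it to 1.07 SD, and baseline adjustment with an assumed correlation of 0.5 to 0.8 lowers it to roughly 0.6 to 0.8 SD. A binary outcome would have a risk-difference width of 0.38 to 0.48.

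The conclusion rests on reading target outcomes as the clinical outcomes, and the adjusted widths rest on correlations that the article does not give. It does not depend on their exact values: with baseline adjustment at one time point, 0.28 SD would need a correlation of about 0.96. The error lies in the stated rationale. It does not show that 75 is an unsuitable size for a pilot whose primary outcomes are about implementation.

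**What to change.** Replace the precision sentence in Aim 3 analytic approach with two statements.

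- **Implementation outcomes.** With about 50 TSC participants observed, the 95% interval for a single-arm proportion is at most 0.28 wide. If only 40 complete the AIM, FIM and IAM ratings, it is at most 0.31 wide (0.25 at a proportion of 0.8).
- **Target outcomes.** Say which outcomes these are. For between-arm differences on continuous scales (50 vs 25), the width is about 0.96 SD unadjusted with full data and 1.07 SD with 40 versus 20. With baseline adjustment it is roughly 0.6 to 0.8 SD for an assumed correlation of 0.5 to 0.8. If an outcome is binary, give the risk-difference width (0.38 to 0.48).

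The cost is a few lines of text and a less favourable stated precision. Enrolment, allocation and the planned analyses stay as they are.

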### Aim 1: Initial qualitative inquiry

#### Aim 1 participants

Aim 1 participants will include 10 adolescents, 10 caregivers of adolescents, and 10 primary care clinicians, including physicians and behavioral health providers, who are working at the affiliated primary care sites. We aim to recruit a sample with at least 50% of adolescent and caregiver participants self-identifying as Black and at least 10% self-identifying as Latinx. Adolescent inclusion criteria are as follows: age 12–18 years; able to understand and converse in English; and evidence of moderate-severe depression (PHQ-9-M >11) (81) and clinically significant sleep disturbance (PHQ-9-M sleep item 3 [“trouble falling or staying asleep”] >2, sleep trouble >50% of days in past 2 weeks). Participants with a life-threatening medical condition requiring immediate treatment or intellectual or developmental disability precluding comprehension of study procedures will be excluded, as will adolescent participants with diagnoses of obstructive sleep apnea, restless legs syndrome, bipolar disorder, a current manic or psychotic episode (per participant or caregiver report or medical record review).

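### A Gaussian mixed model is planned for C-SSRS although entry requires no suicidal ideation: type I error holds, but intervals are moderately too narrow if TSC lowers scores

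*Protocol article*

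**What the plan says.** The Aim 3 analytic approach names one model for all between-arm comparisons of sleep, depressive symptoms "and risk for STB (C-SSRS), are greater among youth randomized to TSC + Sleep Feedback vs. Sleep Feedback Only conditions using linear mixed models". The terms are fixed: "Study arm, time, and their interaction will be included as primary predictors, with random effects for study subject". No binary, ordinal, count or robust alternative is given for C-SSRS.

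On who enters, Aim 3 participants and randomization says "Study inclusion/exclusion criteria are identical to those in Aim 1". Aim 1 requires "evidence of moderate-severe depression (PHQ-9-M >11") and a sleep-item threshold. It sets no ideation or attempt criterion. The earlier open pilot (Initial pilot findings, Methods) did require current suicidal ideation and recruited from a specialty clinic for youth at high risk. Aim 3 recruits at routine well-child visits. Ideation/attempt history is one of three factors on which Aim 3 randomization is balanced.

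On size: "We will recruit 75 adolescents (at least 35% self-identifying as Black; 10% self-identifying as Latinx) to participate in the RCT", and "Adolescents will be randomized using 2:1 allocation (2 TSC + Sleep Feedback: 1 Sleep Feedback Only"), which gives 50 and 25. C-SSRS is collected at baseline and months 1, 3, 6 and 12. STB is a secondary outcome.

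**The concern.** A participant who reports no ideation at baseline cannot improve on this outcome. If many do so, C-SSRS has a floor. A treatment that works then both lowers the mean and shrinks the spread in the treated arm. The planned model, as usually fitted, uses one residual variance for both arms and all visits, and 2:1 allocation lets the larger TSC arm dominate it. The result is a standard error that is too small for the 25 controls.

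The pilot's sample size is justified by interval precision, and its results are meant to inform a fully powered trial. An interval that is too narrow exactly when TSC helps would mislead that use, for the outcome the programme is meant to change. A mean C-SSRS change is also hard to read clinically, because it does not show whether any behaviour or attempt occurred.

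**Working it through.** **The plan's own figure.** The article says that with an intervention sample "of 50 and 5% type I error rate, we will be able to estimate 95% CI widths of no more than 0.28". The Wald width for one proportion at its worst case is 2 × 1.96 × √(0.25/50) = 0.277. The figure reproduces, and it concerns a proportion in one arm, not the C-SSRS comparison.

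**Inputs from the article.** 50 versus 25; five visits; arm, time and their interaction; subject random effects.

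**Assumptions, because the article is silent.** A 0–5 severity score cut from a latent normal variable; exchangeable latent correlation 0.5 (0.7 gave a similar picture); no missing data; baseline share at zero from 10% to 85%; 20,000 trials per scenario.

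**Formula.** With balanced data and time as a factor, the random-intercept model gives the month-12 versus baseline arm-by-time contrast a standard error of √[2s²(1/50 + 1/25)]. Here s² is the residual mean square pooled over arms and visits, on (75 − 2) × 4 = 292 degrees of freedom. On one simulated data set this gave 0.2543, the same as a fitted mixed model.

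**Coverage of the nominal 95% interval**

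| Zeros in TSC, baseline to follow-up | Zeros in control at follow-up | True mean difference | Coverage |
|---|---|---|---|
| no arm difference (30–85% zeros) | same | 0 | 0.948–0.953 |
| 50% to 55% | 50% | −0.15 | 0.943 |
| 50% to 60% | 50% | −0.29 | 0.941 |
| 50% to 65% | 50% | −0.43 | 0.933 |
| 70% to 80% | 70% | −0.26 | 0.933 |
| 85% to 90% | 85% | −0.12 | 0.933 |
| 50% to 75% | 50% | −0.66 | 0.916 |
| 70% to 85% | 70% | −0.38 | 0.917 |
| 70% to 90% | 70% | −0.49 | 0.902 |
| 85% to 95% | 85% | −0.24 | 0.903 |
| 70% to 95% | 70% | −0.58 | 0.884 |
| 10% to 20% | 10% | −0.55 | 0.942 |
| 10% to 35% | 10% | −1.02 | 0.924 |
| 70% to 60% or 50% (TSC worse) | 70% | +0.30, +0.64 | 0.963–0.970 |

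If time enters as a linear slope, coverage is 0.920–0.951.

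**Where the loss comes from.**
- Gaussian data with the same latent shifts keep about 0.95 on this contrast, so the floor is the cause.
- Pooling over arms: let V₁ and V₀ be the variances of change in TSC and control. The true variance is V₁/50 + V₀/25; the pooled one is about [(49V₁ + 24V₀)/73] × 0.06. For illustration take V₁ = 0.75V₀. The true value is 0.015 + 0.040 = 0.055 and the pooled value is (60.75/73) × 0.06 = 0.0499, in units of V₀. The standard error is then √(0.0499/0.055) = 0.95 of what it should be, and coverage is about 0.94.
- Pooling over visits: with near-equal arms (38 versus 37) pooling over arms costs almost nothing, yet coverage is still 0.926–0.933. The rest comes from one residual variance serving both the baseline visit and the less variable follow-up visits in the TSC arm.

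**Check of a remedy.** A subject-level unequal-variance (Welch) interval on change or slope covers 0.947–0.956 in every scenario run.

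**The case against.** The strongest reply is that the pile-up at zero is assumed. The article gives no C-SSRS distribution and does not say which score is analysed, a detail usually left to an analysis plan that is not shown. It describes a depressed sample at risk for STB, so some ideation is likely. This stands in part: the share at zero is an inference from the entry criteria. It does not remove the point, because the article itself names the model, and some loss remains even at 10% baseline zeros (0.924–0.942).

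A second reply is that the loss is small for realistic effects and that the outcome is secondary in a pilot. This also stands, and it limits the weight of the point.

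A third is that logistic and ordinal models were not tested here and can fail with sparse events. With 95% of TSC participants at zero, a visit has no TSC events with probability 0.95⁵⁰ = 0.077. This stands, and it shapes the fix.

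Several stronger readings are tempting but not supported:
- **The test is invalid.** It is not; coverage under no difference is nominal.
- **Coverage falls to about 86%.** A single-visit comparison of 95% versus 75% zeros gives that, but it leaves 2.5 of 50 TSC participants above zero and is not the planned repeated-measures model.
- **Fitted means will leave the possible range.** With time as a factor and complete data they equal the observed cell means, and the article does not say that time is linear.
- **The weekly text-message items share the fault.** These are "items modeled after the Columbia—Suicide Severity Rating Scale (C-SSRS"), but the article does not explicitly assign them a linear model.

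**Conclusion.** The point holds in a limited form. The article commits C-SSRS to a linear mixed model while admitting participants without ideation. With one residual variance, the test of no difference is sound. When TSC lowers scores, the month-12 interval covers about 93–94% for modest effects and 88–92% for large ones. The error depends on closeness to the floor as well as on the change in zeros: 10 points more zeros costs little from 50% (0.941) but more from 85% (0.903). If TSC raises scores, the interval is slightly too wide.

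These figures rest on an assumed 0–5 score, assumed shares at zero, complete data and time as a factor. They concern one secondary outcome. The primary implementation outcomes and the 0.28 width are untouched.

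**What to change.** In the Aim 3 analytic approach, separate C-SSRS from the other secondary outcomes:

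- Define the C-SSRS endpoint. Analyse ideation as binary (any since the last assessment) or as an ordinal severity score, adjusted for baseline ideation, with small-sample or penalised estimation for sparse events.
- If a mean severity score is kept, use arm-specific residual variance or a small-sample-corrected robust (Welch-type) interval. The Welch-type interval is the one shown above to restore about 95%. Because part of the loss comes from pooling over visits, an arm-specific variance should also be allowed to differ by visit.
- Report suicidal behaviours and attempts as counts per arm with exact intervals.
- Keep the planned linear mixed models for PROMIS, PHQ-9-M and actigraphy.

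This changes analysis wording only; participants, visits and sample size stay as they are. The price is slightly wider intervals and possible non-convergence if events are very rare, for which the exact or penalised fallback should be named in advance.

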**Core modules**		
Establishing regular sleep-wake times	Adjust recommendations and increase problem-solving for: • Work, school, and childcare schedules (67). • Characteristics of sleep environment in lower-SES homes and/or neighborhoods (27, 28).	• Flexibility to address youth/family barriers to consistent sleep schedules and routines (66, 68). • Environment plays important role in sleep of youth in lower-SES homes and/or neighborhoods (27, 28).
Learning a wind-down/ wake-up routine		
Improving daytime functioning	Coping strategies for contextual factors, including: • Racism and discrimination for minoritized youth (34, 37). • Limited resources/opportunities for youth of lower-SES backgrounds (69, 70).	• Social and environmental factors contribute to disparities in adolescent sleep health (30, 37, 45). • Problem-solving/coping strategies may be beneficial (13).
Correcting unhelpful sleep-related beliefs	• Assess alignment with family sleep beliefs/preferences • Integrate APA CFI content (64, 65).	• Promotes tailoring of intervention strategies to youth/family culture (66).
Maintenance of behavior change	• Discuss adolescent-specific transitions (e.g., summer to school term, middle school to high school) • Anticipate mood fluctuations	• School start times significantly impact adolescent sleep (48). • Youth at risk for STB may experience mood fluctuations that disrupt sleep gains (65).

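### Aim 3 sleep comparisons cross school term and summer with no school-session term named in the model: avoidable variance in small arms, though no systematic bias

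*Protocol article*

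**What the plan says.** All references are to the protocol article.

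- **School schedule matters for sleep.** In Table 1 (core modules, maintenance of behavior change), the rationale for discussing transitions such as the return from summer to school reads "School start times significantly impact adolescent sleep (48" (the quote stops inside the citation).
- **It is used at randomisation.** Aim 3 participants and randomization: "Random assignment will balance groups on age (middle vs. high school, since school start times typically shift earlier" (the parenthesis continues). The other balancing factors are suicide risk and racial and ethnic background. School session and calendar time are not listed.
- **Timing of assessments.** Actigraphy and the daily diary cover the intervention period, which is 6–8 weeks by the Aim 2 intervention procedures that Aim 3 adopts. Aim 3 measures: "All other secondary outcomes will be collected at baseline (pre-intervention) and at months 1, 3, 6, and 12". This schedule includes the PROMIS sleep scales.
- **Recruitment.** Setting and recruitment describes enrolment around routine well child visits, with no seasonal restriction stated.
- **Model.** Aim 3 analytic approach: linear mixed models, in which "Study arm, time, and their interaction will be included as primary predictors, with random effects for study subject". No session or season term is named.
- **Size.** "We will recruit 75 adolescents (at least 35% self-identifying as Black; 10% self-identifying as Latinx"), with 2:1 allocation, hence 50 versus 25.

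**The concern.** Balancing on middle versus high school deals with differences in start time between participants while school is in session. It does nothing about the change within a participant when term ends or begins, because in summer neither group has a start time. An adolescent whose first and last assessments lie on opposite sides of a boundary shows a change in sleep that has nothing to do with the intervention.

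The model as described leaves that change in the residual. With 25 controls, the arms can also differ by chance in how many participants cross, and in which direction. The actigraphy outcomes are duration, regularity and timing, all of which a change of school schedule could plausibly move. Regularity needs separate thought: depending on how it is computed, a window straddling a boundary may look irregular in either arm. At stake is the precision of the secondary sleep contrasts, which the Discussion says will inform a fully powered trial.

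**Working it through.** **The plan's own figure.** The article states 95% CI widths of no more than 0.28 for an intervention arm of 50. For a proportion at p = 0.5:

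2 × 1.96 × √(0.5 × 0.5 / 50) = 0.277, which rounds to 0.28.

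The figure reproduces. It describes one-arm proportions and does not depend on school session.

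**Inputs from the document:** 50 versus 25; actigraphy over 6–8 weeks; PROMIS at baseline and months 1, 3, 6 and 12.

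**Assumptions (not in the document):** enrolment even over the year; summer of 2.5 months; sleep shifts by d = 30 or 60 min between term and summer; SD of change otherwise 60 min.

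**Actigraphy and diary outcomes, in minutes**

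1. Share of windows containing a boundary (two boundaries a year, 4.345 weeks per month): p = 2 × (weeks / 4.345) / 12. This gives 0.230 at 6 weeks and 0.307 at 8 weeks.
2. Upward and downward crossings are equally likely, so the added variance of start-to-end change is p × d². The SD ratio is √((3600 + p·d²) / 3600).
3. The chance shift in the arm contrast (95% range) is 1.96 × √(p·d² × (1/50 + 1/25)).
4. Without crossings, the 95% half-width of the arm contrast is 1.96 × 60 × √0.06 = 28.8 min.

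| Window | d (min) | p·d² (min²) | SD ratio | Chance shift (min) | Half-width (min) |
|---|---|---|---|---|---|
| 6 wk | 30 | 207 | 1.03 | 6.9 | 29.6 |
| 8 wk | 30 | 276 | 1.04 | 8.0 | 29.9 |
| 6 wk | 60 | 828 | 1.11 | 13.8 | 31.9 |
| 8 wk | 60 | 1105 | 1.14 | 16.0 | 32.9 |

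The chance shift combines with the other sampling error in quadrature. For example, √(28.8² + 16.0²) = 32.9. It is not an extra displacement on top of the interval.

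**PROMIS sleep scores**

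The share whose session status differs from baseline is 2 × min(lag, 2.5) / 12 at months 1, 3 and 6: 0.167, 0.417 and 0.417. At exactly month 12 it is 0, because baseline and visit fall in the same season.

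PROMIS is not measured in minutes, so a simulation expressed the session effect in residual SDs of the change score. It used 50 versus 25, 4,000 replicates per scenario, and enrolment either even or half in summer. The sampling SE without crossings is √(1/50 + 1/25) = 0.245 SD.

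| Session effect (SD) | SD of chance shift, months 1–6 | Variance ratio, unadjusted / adjusted |
|---|---|---|
| 0.25 | 0.03–0.04 | 1.00–1.03 |
| 0.5 | 0.05–0.09 | 1.02–1.10 |
| 1.0 | 0.10–0.17 | 1.14–1.49 |

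Mean bias was about 0 in every scenario. At month 12 the variance ratio was 1.00.

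**The case against.** The strongest reply is that nothing here is misstated. The model sentence calls arm, time and their interaction the primary predictors, which does not exclude covariates, and a condensed article may leave a covariate list to an analysis plan that is not shown. That stands: the point is a request to pre-specify or confirm a term, not the correction of an error. It is also true that these outcomes are secondary in a pilot, and that the size of the session effect cannot be taken from the document.

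A reader might infer more than the document supports:

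- **That the plan contradicts itself by saying summer-to-school transitions disrupt sleep.** Table 1 lists that transition as a topic to discuss. Its remark about disrupted sleep gains concerns mood fluctuations.
- **That the arm contrast is biased.** Arms are randomised concurrently. The expected shift is zero, and the confidence interval already carries the added noise.
- **That sleep minutes at month 3 or 6 are affected.** Actigraphy and diary stop with the intervention. Later sleep outcomes are PROMIS scores.
- **That depression and STB models need the same term.** The document links school schedule to sleep, not directly to those outcomes.
- **That session at entry must be a balancing factor.** Session at entry does not determine who crosses later, and a further factor is a burden in a 75-person trial.

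None of this removes the core: the document's own premise is that school schedule affects sleep, assessments must span term and summer, and the control chosen does not address a change of session.

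**Conclusion.** The point holds as a matter of precision for the sleep outcomes. Under the stated assumptions the SD of change over the actigraphy window rises about 3–14%, and the 95% half-width of the arm contrast goes from 28.8 min to between 29.6 and 32.9 min. For PROMIS at months 1–6 the excess variance is 0–3% for a small session effect, 2–10% for a moderate one and 14–49% for a 1-SD effect. There is essentially none at month 12. The session shift, residual SD, length of summer and enrolment calendar are all assumed; different enrolment timing would change the figures, and a small session effect makes the gain negligible. The primary implementation outcomes and the 0.28 precision statement are untouched. The case for acting rests on the low cost of the remedy rather than on a proven large effect.

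**What to change.** In the Aim 3 linear mixed models for the sleep outcomes, pre-specify a time-varying session covariate taken from the academic calendar:

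- actigraphy and diary nights: school night or not;
- PROMIS assessments: school in or out of session;
- a separate level for adolescents who have left school.

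Taking it from the published calendar keeps it external to treatment, so adjustment introduces no bias. If the analysis plan already contains such a term, a sentence confirming it is enough.

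Regularity describes a run of nights, so a nightly covariate may not attach to it. Keep the planned outcome and add a sensitivity analysis that excludes or flags windows straddling a term boundary.

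No new balancing factor is needed. The cost is one extra model term and a small amount of calendar coding.
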